## Abstract

**BACKGROUND AND OBJECTIVE::**

Venous thromboembolism (VTE), which includes deep vein thrombosis (DVT) and pulmonary embolism (PE), is a common complication in craniotomy patients. The duration of surgery has been identified as a risk factor for the development of VTE. In a pilot study, the use of intermittent pneumatic venous compression (IPC) dramatically reduced the incidence of VTE. Despite randomization, a significant difference in the duration of surgery between the groups limited the validity of this result. The study was underpowered to compensate for this problem. We now present the protocol of a multicenter trial.

**METHODS::**

All patients receive medical compression stockings and low-molecular-weight heparin from the first postoperative day. The therapy group receives IPC stockings intraoperatively. Postoperatively, all patients receive lower-extremity duplex sonography to detect/exclude DVT within the first 7 postoperative days. Contrast-enhanced chest CT is the gold standard for the detection of PE and is performed in cases of clinical suspicion of PE.

**EXPECTED OUTCOMES::**

The incidence of VTE is the primary end point. The distinction between symptomatic and asymptomatic, etiologies, influence of lesion type, duration of surgery, and mortality will be evaluated as secondary end points. The pilot study showed a VTE incidence of 26% in the control group vs 7% in the treatment group. To avoid overly optimistic treatment effect assumptions, we assume VTE rates of 9% and 24% in the treatment and control groups, respectively, and thus calculated a number of 127 patients per treatment group.

**DISCUSSION::**

If this trial shows that intraoperative IPC reduces the risk of VTE to the extent observed in our pilot study (number needed to treat: 5.24), the potential benefit to neurosurgical patients would be significant. The results would potentially influence treatment guidelines by providing the high-quality evidence needed to make robust recommendations.

ABBREVIATIONS:DRKSDeutsches Register Klinischer StudienDVTdeep vein thrombisisGCPgood clinical practiceGCSgraduated compression stockingsLMWHlow-molecular-weight heparinVTEvenous thromboembolism.

## GENERAL INFORMATION

Protocol Title: Intraoperative intermittent pneumatic compression (IPC) reduces incidence of venous thromboembolism (VTE) in patients undergoing craniotomy: Study protocol of a randomized multicenter, single-blind trial.

Registry: German Clinical Trials Register (Deutsches Register Klinischer Studien): DRKS00034190.

Study Dates: June 2024 to June 2027.

Sponsor/Funding Agency: German Research Foundation (Deutsche Forschungsgemeinschaft); Project number 491399287.

Institutional Approvals: Institutional Review Board (Ethics Committee, Faculty of Medicine of the Martin Luther University Halle-Wittenberg, Processing number: 2023-243).

## RATIONALE AND BACKGROUND INFORMATION

Venous thromboembolism (VTE) subsumes deep vein thrombosis (DVT) and pulmonary embolism (PE). Compared with other patient groups, neurosurgical patients are considered to be at an increased risk for these conditions. This is due to presence of malignancy, long duration of procedures, reduced mobility, and direct release of procoagulants such as tissue factors from brain tissue.^1-3^ Up to 50% of patients develop VTE after craniotomy.^4,5^ In the majority of cases, this condition is asymptomatic. However, symptomatic VTE occurs in 7.5% of patients undergoing craniotomy,^6-8^ and even asymptomatic VTE localized to distal muscle veins can progress to symptomatic deep vein thrombosis.^9-13^ This can lead directly and without clinical warning to PE in 7% of affected patients.^14^ Such a PE is caused by DVT in >90% of cases,^15^ occurs in 3.7% of all patients undergoing craniotomy, and is fatal in up to 50% of all affected neurosurgical patients.^5,13,16^ Thus, sufficient prophylaxis of VTE would considerably reduce unnecessary additional risks associated with neurosurgical procedures. Two different approaches have been described to achieve this: pharmacological prophylaxis, eg, by low-molecular-weight heparin (LMWH) or unfractionated heparin on the one hand, and mechanical prophylaxis by graduated compression stockings (GCS) or IPC on the other hand. With IPC, multichambered sleeves are positioned around the lower extremity and sequentially inflated to “milk” the blood from the veins, mimicking the physiological muscle pump. Most trials studying the effect of IPC have implemented this method for prolonged time intervals of several days after surgery; as a consequence of these long time intervals, poor compliance in using the devices has been reported as an issue in several publications.^17,18^

## STUDY GOALS AND OBJECTIVES

The main objective is:

Evaluation of the intraoperative use of IPC to reduce the incidence of VTE in patients undergoing craniotomy.

## STUDY DESIGN

Prospective, randomized, single-blinded multicenter trial.

### Inclusion Criterion

Elective surgery for intracranial pathology via craniotomy.

### Exclusion Criteria

GravidityAge <18 yearsPerioperative administration of blood productsAbnormal blood coagulation (thrombocytes and/or plasmatic coagulation, liver disease, antiplatelet agents)Local leg condition with which the sleeves may interfere, such as dermatitis, vein ligation gangrene, recent skin graft, severe arteriosclerosis, or other ischemic vascular diseaseMassive edema of the legs or pulmonary edema from congestive heart failureExtreme deformity of the legPreexisting thromboembolismClinical signs of deep vein thrombosis

### Sample Size

Sample size calculation for the comparison of the VTE rates in the treatment and control groups is based on a two-sided chi-square test with significance level alpha of 5% and a power of 90%. The pilot study^13^ showed a VTE incidence of 26% in the control group vs 7% in the treatment group. To avoid overoptimistic treatment effect assumptions, we assume VTE rates of 9% and 24% in the treatment and control groups, respectively. This results in 127 patients per treatment group. Assuming a similar dropout rate as in the previous study (approx. 13%), 146 patients per group (292 in total) will have to be recruited (Figure 1).

**FIGURE 1. F1:**
[figure not shown]
Flowchart of the study.

The analysis of the primary end point will be performed by logistic regression using treatment group and treatment center as covariates because of the stratified randomization with respect to treatment center. The logistic regression analysis provides more power compared with the chi-square test mentioned above. Therefore, the planned sample size calculation is conservative.

An interim analysis of the 2 VTE rates will be performed after recruitment of 50% of patients (n = 146) to adapt sample size if necessary. With respect to the specific history of this scientific project, we assign a high priority to the exclusion of underpowering. The intention of the interim analysis is not to stop the trial early because of futility or efficacy.To be assessed for eligibility (n = 350).To be assigned to the trial, ie, recruited (n = 292).To be analyzed (n = 254).

## METHODOLOGY

### Control(s)/Comparator(s)

The control group is treated according to standards of clinical routine. Thus, the incidence of VTE in this group should reflect the status quo in surgical therapy of patients harboring intracranial pathology. Patients in the treatment group are treated exactly the same way with the sole exception of intraoperative administration of IPC. Consequently, any difference in incidence of VTE between both groups should be attributable to IPC.

### Study Population

Patients undergoing craniotomy are at significant risk for VTE, which can hypothetically be lowered by IPC. Thus, undergoing elective surgery for intracranial pathology was chosen as the inclusion criterion. On the one hand, exclusion criteria were chosen to exclude patients in whom VTE incidence might be influenced by additional pathology (eg, spontaneous or iatrogenic disturbances in blood coagulation); on the other hand, patients with conditions that represent contraindications for IPC (according the manufacturer of the device and current guidelines) are to be excluded.

### Treatments/Procedures

All patients will receive GCS perioperatively and LMWH starting on the first postoperative day. Both groups will receive IPC sleeves for the complete duration of the surgical procedure. The sleeves will be put on by trained personnel during positioning of the patient; they are standard, CE-certified equipment, which is specifically approved for use in the prevention of VTE. The device Flowtron ACS900 (Arjo) will be used in all patients. In the *control group*, it will not be activated; otherwise, they are treated exactly the same way.

### Additional Treatments

In case of evidence of thrombosis or PE, drug therapy is initiated according to general practice guidelines as established by the respective center. If thrombosis is detected, compression therapy is also started accordingly.

### Outcome Measures

Primary end point:Incidence of VTESecondary end points:Proximal and distal deep vein thrombosis, symptomatic vs asymptomatic VTE, muscle vein thrombosis, central venous catheter–related thrombosis, PE, death, influence of lesion type, and duration of surgery.

### Data Collection

The Coordination Center for Clinical Trials will be responsible for data management and data archiving. The data and essential trial sponsor documents (Master File) will be managed and archived according to existing standards and regulations, in a data format allowing long-term preservation and future reuse. The sites will also be instructed to archive respective essential documents (investigator site file, CRFs, and source data) according to existing standards and regulations. The trial is registered with full description at the German Clinical Trials Register (Deutsches Register Klinischer Studien, DRKS).

## DISCUSSION

IPC exclusively during the surgical procedure and in addition to standard prophylaxis consisting of GCS and LMWH would avoid such problems. In a pilot study,^13^ we evaluated such a novel shortened IPC regimen. The results showed a statistically significant risk difference of 19.1% [95% CI 5.9%-62.1%] and number needed to treat of 5.24 between patients with additional intraoperative IPC and patients only receiving standard prophylaxis. Despite randomization, a significant difference between duration of surgery in the groups limited the validity of this result. The study was underpowered to compensate for this issue.

As the larger number of patients needed for the new trial exceeds the capabilities of a single center, we designed a multicentric trial with financial support by German Research Foundation (Deutsche Forschungsgemeinschaft). If by this trial intraoperative IPC is confirmed to reduce the risk for VTE on the scale observed in our pilot study, the potential benefit for neurosurgical patients would be considerable. The results would potentially influence treatment guidelines in providing the needed high-quality evidence for robust recommendations.

## TRIAL STATUS

The current status of the trial is in the preimplementation stage.

## SAFETY CONSIDERATIONS

### Assessment of Safety

Adverse events associated with IPC will be monitored and reported according to good clinical practice (GCP) principles and regulatory requirements. Assessment of safety does not constitute an end point of this study.

Our pilot study indicated that application of IPC during the surgical procedure is safe, and that it reduces VTE risk considerably.^18^ Previous studies have not reported any severe complications by use of IPC. For the proposed additional, exclusively intraoperative use, there is currently no evidence. The procedure is therefore not considered standard practice. Thus, it is not unethical to withdraw IPC from patients of the control group, which will receive medical care according to local standards. In addition, even patients of the control group will benefit from improved detection rates of VTE by the Doppler sonography each patient will receive (not part of standard clinical practice). Evidence on the efficacy of the easy-to-implement regimen would, however, significantly affect clinical care and ultimately benefit patients. An independent data safety monitoring board will closely review safety data on a regular basis and will make recommendations regarding further conduct of the trial, eg, to continue or hold enrollment, to amend protocol, or to stop the study early.

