### Duration of Intervention per Patient

All patients (both treatment and control groups) are treated with GCS from patient positioning until the fifth postoperative day, combined with subcutaneous administration of low-molecular-weight heparin, which is started with the first postoperative day and continued until discharge.

All trial-related investigations (intervention and follow-up) are limited to the single stay of each patient for their surgery. During the surgical procedure, IPC is applied. The primary end point (incidence of VTE) is then evaluated by Doppler sonography within 7 days after surgery (Table). No further follow-up is planned.

**TABLE. T1:** Trial-Related Investigations

Time point	Trial measure
Perioperatively	Graduated compression stockings
Surgical procedure	IPC (activated/not activated)
Starting on first postsurgical day	LMWH according to the specific standards of the respective center
Surgery to 7th postoperative day	Doppler-sonography: primary (incidence of VTE) and secondary end points
Surgery to 7th postoperative day	Assessment of safety

IPC, intermittent pneumatic compression; LMWH, low-molecular-weight heparin; VTE, venous thromboembolism.

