## DATA MANAGEMENT AND STATISTICAL ANALYSIS

### Methods Against Bias

Bias in assessment is addressed by a randomized single-blinded study design. Randomization will be stratified with respect to treatment center and will be performed centrally via an internet-based automatic system at the local Coordination Centre for Clinical Trials. The personnel performing Doppler sonography and diagnosis of PE will be blinded to group status of all patients; in addition, sonography will be performed according to Deutsche Gesellschaft für Ultraschall in der Medizin guidelines (Untersuchung der tiefen Beinvenen und Beckenvenen, Grundlagen und Technik).^19^ All ultrasound examiners involved in the study will meet and establish consensus on the definitions of DVT and its subtypes before the study starts. Patients are blinded to the randomization. To ensure this and to enable identical treatment in all patients of the treatment group, the same type of IPC device (Flowtron ACS900 (Arjo)) will be used in all centers taking part in the study. To avoid a center bias, all centers participating in the study will be limited to a maximum number of 100 patients over the duration of the study. However, the centers will be instructed to recruit their patients from a consecutive series to not introduce selection bias. As a consequence of this concept, there is a limit of 100 patients over the duration of the study per center despite the obvious ability of certain centers to contribute a higher number of patients.

The study will be analyzed according to the intention-to-treat principle to avoid attrition bias. It is registered prospectively in the DRKS (German Register of Clinical Studies; DRKS00034190) and will be reported according to CONSORT (Consolidated Standards of Reporting Trials).

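### Stated adverse event capture is limited to events judged to be associated with IPC, so recording of leg events can differ between the arms

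*Protocol article*

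**What the plan says.** Under Safety Considerations (Assessment of Safety), the protocol article gives its only description of which adverse events are captured: "Adverse events associated with IPC will be monitored and reported according to good clinical practice (GCP) principles and regulatory requirements". It adds: "Assessment of safety does not constitute an end point of this study". It also sets up oversight: "An independent data safety monitoring board will closely review safety data on a regular basis". That board may recommend holding enrollment, amending the protocol or stopping early.

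Under Treatments/Procedures, "Both groups will receive IPC sleeves for the complete duration of the surgical procedure". In the control group the device is fitted, but "it will not be activated; otherwise, they are treated exactly the same way".

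Under Methods Against Bias, patients are blinded, and "The personnel performing Doppler sonography and diagnosis of PE will be blinded to group status of all patients". No other role is said to be blinded. The Study Design section calls the trial single-blinded.

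Two other places bear on the point. The Table under Duration of Intervention per Patient lists "Assessment of safety" from surgery to the seventh postoperative day, without restriction by arm or by cause. Outcome Measures names PE, death and several thrombosis categories as secondary end points.

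The Assessment of Safety section also says that the pilot indicated safety and a considerable reduction in VTE risk. It then says: "For the proposed additional, exclusively intraoperative use, there is currently no evidence".

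**The concern.** The stated rule puts a causal filter ahead of recording. Someone must first decide that an event is associated with IPC, and only then is it monitored and reported. If that person knows whether the pump ran, the decision can depend on the arm. A pressure mark or nerve deficit may be put down to the device when it was inflating and to positioning when it was not.

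The inactive sleeves in the control arm are what would let the trial separate the effects of compression from background and positioning effects. The Control(s)/Comparator(s) section uses this reasoning for efficacy: the arms are treated alike, so a difference in VTE is attributed to IPC. The reasoning carries over to harms only if events are recorded alike in both arms.

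Two things are at stake: the board's ability to read a between-arm table of local leg events, and the trial's ability to report harms fairly alongside a benefit that it hopes will influence guidelines.

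**Working it through.** No figure in the plan is wrong on this point. The check is a comparison of sections, followed by a sense of scale.

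**Sections side by side**

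1. Scope of capture: Assessment of Safety restricts it by cause. The Table gives a window (surgery to day 7) with no restriction by cause or arm. The two do not match.
2. Exposure: Treatments/Procedures gives both arms the sleeves for the whole operation. Only activation differs.
3. Blinding: Methods Against Bias covers patients and the Doppler and PE personnel. Nothing says who records adverse events or judges their cause, and nothing says that those people are blinded.
4. Harms outside the filter: PE, death and thrombosis subtypes are secondary end points in both arms and do not depend on attribution to IPC.

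The exposed part is therefore local leg events (skin, pressure, nerve), which are not end points and reach the record only through the adverse event rule.

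**Scale**

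The Sample Size section gives n = 146 recruited per group. The rate r of leg events is not in the documents. I assume 3% in both arms, with a range of 1% to 5%.

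- Expected events per arm = n × r: 146 × 0.03 = 4.4; 146 × 0.01 = 1.5; 146 × 0.05 = 7.3.
- If a fraction c of events passes the filter in each arm, the spurious expected difference is n × r × (c_active − c_control). It is zero when the fractions are equal and at most n × r, that is 4.4 (1.5 to 7.3), when attribution is complete in one arm and absent in the other.
- Extreme case at 3%, 4 vs 0 events: two-sided Fisher p = 2 × C(146,4)/C(292,4) = 0.12.
- Extreme case at 5%, 7 vs 0 events: p = 2 × C(146,7)/C(292,7) = 0.015.
- Opposite extreme, with no event attributed in either arm: 0 vs 0, and real events go unseen.

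These are bounds, not predictions.

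**What full capture could deliver**

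- Zero events in 146 patients gives a one-sided 95% upper limit of 1 − 0.05^(1/146) = 2.0%.
- With assumed true rates of 2% control and 6% active (146 × 0.02 = 2.9 and 146 × 0.06 = 8.8 events), a two-sided 5% comparison has about 41% power. With 2% and 8% (2.9 and 11.7 events) it has about 65%.

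Complete recording removes the bias but does not make the comparison precise.

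**The evidence statements**

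The Discussion describes the pilot as an evaluation of IPC limited to the surgical procedure and added to standard prophylaxis. Assessment of Safety credits the pilot with indicating safety and benefit, then denies that any evidence exists for exclusively intraoperative use. As written, these cannot all be true.

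**The case against.** The strongest reply is that one sentence in a condensed article is being read too hard. Event definitions, causality fields and board tables normally sit in the full protocol, the CRF and the board charter, which are not shown. The sentence also invokes GCP and regulatory requirements. This stands as far as missing detail goes. It does not dispose of the point, because the sentence states a scope, and that scope is narrower than the Table's. If the full protocol is broader, the published sentence misdescribes it.

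A reader might infer that the board will have no control-arm rate at all. The documents do not support that. The Table's safety assessment is not limited to one arm, PE, death and thrombosis are collected in both, and the board is to receive safety data without further restriction.

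A reader might also infer that an event in a control patient cannot be called IPC-associated. That is too strong as well. Controls wear the sleeves, and the Table describes the measure as IPC, activated or not activated, so an injury under an inactive sleeve can fall within the phrase. The difficulty is greater for harms of active compression.

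That staff know the allocation is an inference from single-blinding and the list of blinded roles; it is not stated. Narrow capture may also be deliberate, since the device is CE-certified for VTE prevention and safety is not an end point. Finally, the inconsistency about prior evidence is a wording matter in the ethical rationale and does not itself show that the capture rule is wrong.

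**Conclusion.** The point holds in a limited form. The stated rule makes recording depend on a causal judgement by people not said to be blinded, in a design where only pump activation separates the arms. Recording of local leg events can therefore differ by arm and bias the between-arm harm data that the board reviews. PE, death and thrombosis are not affected.

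The size cannot be taken from the documents. Under the assumed 3% rate it concerns about 4 events per arm (1.5 to 7.3 for 1% to 5%), and the distortion lies anywhere from none to all of them. The conclusion rests on two assumptions: that whoever attributes events may know whether the pump ran, and that the published sentence reflects the operative rule. The change is worth making because the trial is still at the preimplementation stage and events that were never recorded may not be recoverable later.

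The conflict over prior evidence is a separate, smaller point that needs a wording correction.

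**What to change.** Replace the scope in Assessment of Safety with a rule along these lines: from surgery to postoperative day 7, a short prespecified list of leg events under the sleeves (for example skin injury, pressure injury and nerve deficit), as noted in routine care, is recorded in both arms regardless of suspected cause; suspected relation to IPC is entered in a separate field; the board receives these events tabulated by arm. Align the section with the Table, so that scope and window agree.

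The cost is a little more data entry and one table by arm. No added visit or examination is asked for. Recording serious adverse events of every cause, or adding a dedicated leg or nerve examination, would be a larger step and is not needed to remove this bias. The sponsor should report the comparison as imprecise at 146 per arm.

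Separately, reconcile the no-evidence sentence with the accounts of the pilot in the same section and in the Discussion, for instance by saying what evidence the pilot gave and how it was limited.
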